## Method/design

### Design and participants

We will employ a SW-RCT with 30 outpatient SUD treatment clinics who serve approximately 2000 clients with OUD per year to test whether CARE improves treatment process quality and recovery outcomes over treatment as usual. The study will benefit from multiple sources of data to test study aims, including state administrative data, client-reported survey and eTPA8 data, and staff interview and survey data. Therefore, this will be a robust study of the implementation of a measures-driven QI approach for SUD treatment. Figure 2 shows the stepped-wedge design. Five clinics will start CARE every 6 months over 3 years; therefore, there are 6 steps, each with 5 clinics randomly assigned to 1 of the 6 steps.

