### Measures and materials

#### Data sources

The NYS OASAS registry of all admissions and discharges (irrespective of payer) to licensed addiction treatment facilities—the Client Data System (CDS)—forms the basis of our administrative data set. The CDS will record all treatment episodes that occur in the 30 clinics we include in this study, providing a rich source of data. All licensed providers of SUD treatment in NYS are mandated to submit admission and discharge data into the CDS. NYS OASAS tracks each individual by unique identifiers. When clients enter treatment, providers enter information on demographics, level of functioning (e.g., health status, comorbidities), criminal justice status, recent history and frequency of substance use, and recent SUD treatment history. Upon discharge, providers enter information on functional status (e.g., employment, housing), source of payment for treatment (e.g., self-pay, Medicaid, private insurance), criminal justice involvement during treatment, hospitalizations, and use of ED services. Additionally, the discharge information has type, frequency (i.e., number of sessions), and intensity of SUD treatment as well as discharge status (discharge disposition and goal achievement). NYS Medicaid claims will supplement the administrative dataset by providing data on OUD medications and health services use (e.g., ED visits). We will link clients in Medicaid to the CDS using the NYS OASAS identifier augmented, in cases where there were no exact matches, by searching for same treatment events that were recorded in each database. Additionally, we will employ probabilistic matching techniques to account for data entry errors on elements of the OASAS identifier. Our link rate in previous studies among OUD individuals in Medicaid is 90% [47].

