#### Measures

Based on treatment episode and client admission information in the CDS and claims information in Medicaid, clinic level covariates, quality, and outcomes data will be computed in 6-month assessment windows. Client level covariates from the CDS will include frequency of use, injection drug use, age, gender, race/ethnicity, education, residential stability/homelessness, and psychiatric comorbidities at admission. Medicaid claims will be used to identify OUD medications, various health conditions based on ICD-10 diagnosis fields; healthcare episodes based on procedure, rate and NDC codes; and cost based on Medicaid payments for claims and encounters. Clinic rates of 6-month retention will be computed from admission and discharge dates in the CDS. OUD medication initiation and adherence will use data from Medicaid pharmacy claims during an episode. Initiation will be a new OUD medication pharmacy claim within 30 days and adherence will be computed using the NQF 3175 definition [51–53]. Overdoses will be identified by CDC defined combinations of diagnoses and acute care procedure codes [54, 55]. All-cause ED visits will be defined by procedure and rate codes. HCV infections will be defined by diagnoses during any hospitalizations or on two outpatient claims [56, 57]. Costs of healthcare services will be drawn from Medicaid claims and encounter data.

Provider-level covariates will also be calculated. SUD program characteristics will be drawn from computing provider-level statistics from claims as well as from state databases that contain addresses, affiliations, and licensing information. Provider variables will include geographical location, annual census, and hospital affiliation. Geographical information of provider location will be drawn from the Area Health Resources File: poverty, population density, ethnic/racial population, and health professional availability.

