### Analysis and power

The primary aim of this study is to test whether CARE is associated with greater use of pharmacotherapy for OUD, longer retention in care, and improved recovery outcomes (e.g., reduced drug use). We will employ multiple convergent analytical methods to (a) examine CARE implementation and (b) test association between CARE and OUD treatment outcomes. Analyses will begin with examination of distributions of variables and transformations where appropriate, examination of patterns of missingness, and application of formal imputation methods [77–79] if deemed essential to project aims. Analyses for Aims 1, 2, and 3 will utilize general linear mixed models (GLMM) for stepped-wedge designs [80–85]. For example, to test the effect of CARE on treatment process quality measures (i.e., initiation and adherence to OUD medications, in-treatment symptom and therapeutic progress, 6-month treatment retention) and recovery outcomes (substance use, overdoses, self-reported health status, HCV infection, and ED visits), we will employ stacked difference-in-difference models that test for within and across clinic changes while adjusting for secular trends across time [80, 86, 87]. The models will take the form: *Y*_*ikt*_ = *μ* + *X*_*kt*_*θ* + *β*_*t*_ + *Z*_*ikt*_ + *α*_*k*_ + *e*_*ikt*_, where *β*_*t*_ is a fixed effect for time, *Z*_*ijk*_ is a matrix of covariates measuring individual, geographical, and clinic characteristics for person *i* in clinic *k* at time *t, X*_*kt*_ is an indicator for intervention in clinic *k* at time *t* (coded 0 for baseline then 1 from when intervention begins in clinic through end of study), and *θ* is the treatment effect. *Y*_ikt_ represents a matrix of binary variables: treatment process quality measures (i.e., pharmacotherapy initiation and adherence, in-treatment symptom and therapeutic progress, treatment retention) and recovery outcomes (i.e., substance use, overdoses, self-reported status, HCV infection, and ED visits). We will estimate the effect of CARE (*θ*) while controlling for secular trends (*β*) and adjusting for clustering within clinic (*α*_*k*_) using robust standard errors. We will also conduct a set of falsification tests. These will include (1) testing for variation in program and client characteristics across time of enrollment; (2) examination of variation across study time in the study outcomes for clinics not participating in the study; and (3) examination of variation in intervention effect based on clinics’ baseline levels of quality measures (e.g., comparing top third to bottom third in quality of care at baseline).

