## Discussion

This study will provide a robust examination of the implementation of a measures-driven QI approach for SUD treatment. We will be able to provide insight into whether a multicomponent intervention that includes clinical training, training and support on QI processes, external facilitation, and an electronic client outcomes monitoring system improves quality and recovery outcomes. The study benefits from a strong academic-state partnership, an external facilitation model guided by the i-PARIHS implementation science framework, multiple sources of data to examine impacts of the intervention, as well as tools and trainings developed with input from a variety of stakeholders and a pilot during the first phase of this project.

The study team is currently finalizing clinic recruitment and randomization with plans to start the first five clinics in the intervention in December 2020 and January 2021. The ongoing COVID-19 pandemic has forced a shift in SUD treatment service delivery, which has traditionally relied heavily upon in-person services. Outpatient treatment clinics have had to rapidly and fundamentally change their service delivery models due to physical distancing mandates and new COVID-19 safety protocols. For example, programs have needed to change their work flows to accommodate telepractice for induction and management of medications for OUD, provide individual and group counseling via telemedicine, reduce reliance on drug screening (i.e., toxicology testing), and employ new strategies for treatment engagement. Therefore, while the pandemic continues, this study will not only have to adjust some of its facilitation and training activities to be done remotely rather than in-person, but we will also tailor facilitation to assist clinics in improving quality of care in the context of COVID-19 shifts in service delivery and workflows. We will carefully document changes to our protocols and clinic procedures as the COVID-19 pandemic continues to affect NYS and our participating project sites.

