While there are a number of strengths in this study, we acknowledge the following possible exogenous and endogenous threats to validity. First, administrative data is incomplete. We rely significantly on administrative data to increase the efficiency of our research study that tests the impact of CARE in 30 clinics on treatment quality measures (e.g., pharmacotherapy use, retention) and outcomes (e.g., relapse). While there is strong precedent for using administrative data for research [99–106], these data will not capture all aspects of client experience (e.g., substance use, social consequences). To address the limitation, we are using a mobile platform that allows for collection of research data from a subsample of participants. These data will allow us to further study the intervention impact on recovery outcomes not captured in the administrative data.

In addition, there may be variability in the effect of the intervention due to variation in individual clinic capacity to integrate QI practices within their organizational structure. It will be critically important for future dissemination efforts to understand factors implicated in the implementation of CARE. While the study has adequate statistical power to detect a main effect, it will be important to understand the variability in effect across clinics. To address this, we will incorporate the embedded mixed-methods component of the study examining staff experiences. Additionally, we will explore potential intervention-related factors by conducting a series of post hoc analyses.

Finally, though the SW-RCT design offers a number of benefits, clinics will be randomized to step at the start of the trial with start dates staggered across 3 years. Therefore, it may be challenging to retain recruited clinics in the study while they wait to start the intervention. To reduce clinic attrition, we will employ strategies recommended in the stepped-wedge trial literature (e.g., keep recruited sites informed of progress, hold regular pre-intervention meetings) [107]. Also, recruited clinics will sign a study agreement indicating they understand the randomization procedures and timeline.

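### The CARE indicator is tied to when CARE begins in each clinic and does not name the randomised step, so the effect estimate loses the protection of randomisation if clinics start late or withdraw for reasons linked to their outcomes

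*Protocol article*

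**What the plan says.** Design and participants sets the schedule: "Five clinics will start CARE every 6 months over 3 years; therefore, there are 6 steps", with five clinics randomly assigned to each step. The Discussion adds that "clinics will be randomized to step at the start of the trial with start dates staggered across 3 years". The step is therefore the randomised quantity, and it is fixed before any clinic begins.

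Analysis and power defines the exposure variable of the main model differently. X_kt is "coded 0 for baseline then 1 from when intervention begins in clinic through end of study". The assigned step is not mentioned there, and no section states analysis by assigned step or by intention to treat.

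On departures from schedule, the Discussion accepts that "it may be challenging to retain recruited clinics in the study while they wait to start the intervention" and lists ways to reduce attrition. It gives no rule for coding a clinic that starts late or withdraws.

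On data, the Data sources section says "The CDS will record all treatment episodes that occur in the 30 clinics we include in this study" and that "All licensed providers of SUD treatment in NYS are mandated to submit admission and discharge data into the CDS". Under Measures, "outcomes data will be computed in 6-month assessment windows", which is the length of one step.

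**The concern.** The order in which clinics cross over is what makes a stepped wedge a randomised comparison. If exposure follows the clinic's own start, a clinic that postpones contributes its delayed windows as control time. A clinic that withdraws while waiting would, if its data are kept, contribute control time to the end.

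Starting CARE needs leadership backing, champions and a weekly change team. A clinic short of staff or disrupted by the pandemic may be unable to start on time, and the same trouble may move its retention or medication rates. Clinic circumstances would then help decide which windows count as exposed. Fixed time effects and clinic effects do not remove this, because the disturbance is specific to a clinic and to a window. Robust standard errors change the interval, not the estimate.

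**Working it through.** **1. The plan's own figure.** Inputs from Analysis and power: 30 clinics, 6 crossover points of 5 clinics, m = 132, base rate 0.25, ICC 0.20, alpha 0.01, power 0.80. Assumptions: two-sided test, 7 windows (one baseline plus six), and m counted per clinic and window. These reproduce the plan's figure.

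- Within-clinic variance of a window mean: (1 - 0.20) × 0.25 × 0.75 / 132 = 0.001136.
- With X switched on at the randomised step and adjusted for clinic and window, the residual sum of squares of X is 16.67. So SE = sqrt(0.001136 / 16.67) = 0.00826. The Hussey-Hughes formula gives 0.00824.
- Multiplier: 2.576 + 0.842 = 3.417.
- Detectable difference: 3.417 × 0.00824 = 0.0282, or 2.8 pp as stated.

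This calculation assumes that all 30 clinics start at their randomised step.

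**2. Departures unrelated to outcome.** With a true effect of 2.8 pp and 10%, 20% or 30% of clinics one window late at random, own-start coding still averages 2.8 pp in simulation. With no true effect it averages about zero. There is no bias in this case.

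**3. Departures related to outcome, no true effect.** Clinic-window means were simulated with the variance above. Each clinic-window had probability 0.1, 0.2 or 0.3 of a temporary 5 pp dip in retention. These rates and sizes are assumptions.

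| Assumed link between dip and start | Own-start coding, pp (dip probability 0.1 / 0.2 / 0.3) |
|---|---|
| Dip in the scheduled start window always postpones, while it lasts (about 3 / 6 / 9 clinics) | +0.7 / +1.4 / +2.0 |
| Same, but a dip postpones only 25% of the time | +0.2 / +0.3 / +0.4 |
| Dip in the window before the start postpones, while such dips persist | -0.15 / -0.3 / -0.45 |

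Repeat runs of the last cell gave -0.42 to -0.47. Coding by randomised step stayed at about zero in every row. Using m = 33 instead of 132 left the first row almost unchanged (+0.7 / +1.4 / +1.9).

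**4. Withdrawal while waiting, no true effect.** Suppose withdrawn clinics are kept and coded 0 throughout, and their retention falls 1 pp per window more than the others'. With 10% or 20% withdrawing, own-start coding gives +0.8 or +1.3 pp, and rejects 4.7% or 17% of the time at nominal 1% (model-based standard errors). At 0.5 pp per window it gives +0.4 or +0.7 pp. The estimator is linear in the outcomes, so the sign reverses if the withdrawing clinics were improving. Step coding stays at about zero and rejects about 1% of the time.

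**5. Price of step coding.** If a random fraction f of clinics starts one window late, the late cells carry 12.5 / 16.67 = 0.75 of the effect's weight. The expected estimate is therefore 2.8 × (1 - 0.75f):

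- f = 0.1: 2.6 pp, simulated power about 0.71
- f = 0.2: 2.4 pp, simulated power about 0.60
- f = 0.3: 2.2 pp, simulated power about 0.53

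If a fraction f never starts, the expected estimate is 2.8 × (1 - f): 2.5 pp at 10% (power about 0.67) and 2.2 pp at 20% (about 0.55).

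**The case against.** The sentence can be read as the scheduled start. Design and participants has clinics starting at their assigned step, and if the schedule is kept the two codings are identical. The indicator also stays at 1 to the end of the study although CARE lasts one year, so a clinic that stops after starting remains exposed. That points away from a fully as-treated analysis. Handling of late starters could sit in the full protocol, and step coding costs power.

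Much of this stands. Own start is the plain reading but not the only one, and the harm depends on departures. It does not dispose of the point, because the article does define the variable, and does so without reference to what was randomised.

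A reader might infer four stronger things that the document does not support:

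- **The randomised comparison is lost.** It is not, if clinics keep to schedule or depart for reasons unrelated to outcome.
- **The bias always favours CARE.** Size and sign depend on the assumed mechanism. Only a retention-like outcome was simulated, not medication or ED visits.
- **Withdrawn clinics count as control.** The article does not say so; they might instead be dropped.
- **Departures are already planned**, from the statement of "plans to start the first five clinics in the intervention in December 2020 and January 2021". Those are planned dates for one step, adjacent months within a 6-month window, and show no clinic leaving its step.

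**Conclusion.** The point holds in conditional form. The stated coding follows each clinic's start and does not name the randomised step. The article itself foresees difficulty in keeping clinics while they wait. If late start or withdrawal is related to a clinic's outcome course, theta is not protected by randomisation. With assumed 5 pp dips and no true effect, the error ran from about -0.4 to +2.0 pp against a detectable difference of 2.8 pp, while step coding stayed at about zero. The rates, dip sizes and mechanisms are assumptions, since the article gives no departure rate. With no departures, or departures unrelated to outcome, the bias is nil.

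**What to change.** In the primary analysis, define X_kt by the clinic's randomised step date: 0 before it and 1 from it to the end of the study, whatever the actual start. State that all 30 randomised clinics stay in the CDS- and Medicaid-based outcomes, including any that start late or withdraw. Mandatory registry reporting makes this feasible. Check that the clinic participation agreement covers use of administrative data after withdrawal. Report own-start coding as a secondary analysis. If scheduled start was always meant, one sentence confirms it.

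The drafting cost is small. The statistical cost is the dilution and loss of power shown in the working, which should be acknowledged next to the 2.8 pp figure, since that figure assumes full adherence to the schedule.

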Utilization of data and metrics as well as implementation of QI processes will require SUD clinics to make significant changes at various levels within their organizations. This study will use an external facilitation model guided by the Integrated Promoting Action on Research Implementation in Health Services (i-PARIHS) framework to support clinic implementation of QI processes [38, 39]. i-PARIHS posits that optimal implementation occurs when practice facilitation promotes the acceptance and use of a new innovation by tailoring it to the recipient’s specific needs [39, 40]. Facilitators are the active ingredient that help navigate teams through complex change processes by addressing (a) the fit within the existing clinic, (b) motivations, beliefs, goals, and resources of intervention recipients, and (c) the inner and outer implementation context. In QI projects, the goal of facilitation is typically to support sustained focus and achievement of specific goals; facilitators work to enable individuals and teams to analyze, reflect, and change their way of working [41].

Patient monitoring tools are central to managing quality of care for other behavioral health conditions yet are not often systematically used in SUD treatment programs. For example, a hallmark of collaborative care models for depression is the use of evidence-based assessment tools, like the PHQ-9 depression scale, for ongoing monitoring and treatment adjustments. We recently developed an 8-item tool for SUD clinic settings, the Treatment Progress Assessment-8 (TPA8), that monitors SUD symptoms and treatment progress indicators that are associated with clinical outcomes and relapse [42]. We have been in the process of developing an electronic version, the eTPA8, to ease administration to clients as well as to provide a robust data reporting system that SUD clinics can use in client care as well as QI efforts. The eTPA8 will be part of the intervention package in the current study to support QI practices.

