In this paper, we describe a study protocol for a stepped-wedge randomized controlled trial (SW-RCT) stemming from a state-academic partnership that will test a multicomponent, clinic-level intervention, called Coaching for Addiction Recovery Enhancement (CARE). We will test whether CARE improves treatment process quality and recovery outcomes over treatment as usual, particularly for OUD. The SW-RCT design was selected mainly because the intervention is conducted at the clinic-level and, from a resource perspective, it would be impractical to provide the intervention to all clinics at once given the facilitation model being utilized. Further, the stepped-wedge design was seen as more acceptable and ethical for key program stakeholders (notably the single state agency that regulates SUD treatment [SSA]) due to the potential benefits from the resources being provided as part of the intervention package (e.g., training support from the SSA) compared to a parallel randomization design. The CARE intervention includes the following components: (1) staff clinical training and tools, (2) quality improvement and change management training, (3) external facilitation to support implementation and sustainability of quality improvement, and (4) the eTPA8 client-reported treatment progress tool to support data-driven decision making and clinic-level quality measurement. See Fig. 1 for our intervention conceptual model. We describe intervention components in more detail in the method section. Study aims and hypotheses are the following:
Aim 1: Test the effect of CARE on treatment process quality measures and recovery outcomes.
Hypothesis 1: CARE will improve clinic-level rates of treatment process quality measures (i.e., initiation of and adherence to OUD medications, in-treatment symptom and therapeutic progress, 6-month treatment retention) and recovery outcomes (i.e., substance use, overdoses, self-reported health status, hepatitis C infection [HCV], and emergency department [ED] visits).Aim 2: Examine association of changes in the eTPA8 client-reported treatment progress tool with treatment retention and substance use outcomes.

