### Description of the CARE intervention

The overall goal of the multicomponent, clinic-level CARE intervention is to help SUD clinics make improvements in rates of OUD medication initiation and adherence, rates of 6-month retention, and recovery outcomes by providing training and implementing QI procedures with support from an external facilitator. The CARE intervention will be 1-year-long for each participating clinic. Guided by phased implementation models [46], ‘active’ intervention by the external facilitator will take place during the first 6 months (see Table 1). The second 6 months will be a sustainment phase in which clinics continue QI activities with limited facilitator support (e.g., troubleshooting). Guided by the i-PARIHS model, facilitators will support clinics in making adjustments to clinical and program procedures. They will tailor their approach to fit with each clinic’s workflow while addressing staff motivations and resources and attending to the inner and outer context of each clinic.

**Table 1 Tab1:** CARE intervention components during 6-month active phase

CARE component	Rationale	Execution	Target
Training/tools on OUD medications, shared-decision making, and person-centered care	Increase knowledge, skills, and, attitudes about evidenced-based practices to improve client outcomes	1-h, interactive web-based trainings; moderated discussion with external facilitator; guides/tools for OUD medication and shared decision making	All clinic staff
Leadership engagement	Gain buy-in from executive level of the organization to ensure resources available for QI processes and clinical practice change	1.5-h kick-off meeting with study team and ongoing updates and engagement from external facilitator and champions	Clinic executive leadership
Establish clinic champion(s) and change team	Structured team to conduct QI and change management activities	Executive and clinic leadership select champion(s) with support from facilitator	Identified clinic staff
Training on QI and change management	Improve numeracy, data management, and quality improvement knowledge	45-min web-based training plus external facilitator provides training to champion; champion provide training to change team	Clinic champion(s) and change team

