Ongoing QI and change management activities	Improve clinics’ ability to engage in data-driven, structured QI cycles and ongoing data monitoring	Weekly 1-h change team meetings lead by clinic champions and supported by the external facilitator	Clinic champion(s) and change team
eTPA8 client-reported treatment progress tool	Improve clinical outcomes and capacity for technology-based data monitoring and QI	Clients complete the eTPA8 every 2 weeks; staff monitor reports for use in clinical decision making; change team uses reports for QI	All clinic staff, champions, change team

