Client-reported treatment process improvement will be computed from change scores on the eTPA8 from baseline to latest administration. Further, the client-self reported mobile survey will include the following measures: (1) past 2-week use of opioids and other substances based on the Addiction Severity Index (ASI) [58], (2) substance use consequences based on the Short Inventory of Problems-Revised (SIP-R) [59], (3) health-related quality of life based on the first item of the SF-36 [60], (4) functional outcomes using the Treatment Effectiveness Assessment [61], past 30-day employment, incarceration, housing status based on the ASI, (5) a visual analog scale measuring cravings to use substances [62], and (6) demographics.

Staff surveys will include measures on practice change capacity (i.e., the change process capability questionnaire) [63, 64], the Opinions About MAT Survey [65], knowledge and perceptions about person-centered care and shared-decision making, and use of data and quality metrics. An interview guide for staff qualitative interviews will be created to reflect the dimensions of the i-PARIHS model (e.g., inner context) [66].

The marginal cost of the CARE intervention will be estimated to inform future intervention development and implementation. We will collect detailed data on staffing and other resources to inform micro-costing computations and estimates of the marginal costs of deploying CARE under real-world conditions [67–69]. Cost data collection will follow generally accepted practice in cost-effectiveness research [67, 68]. In addition, the cost collection procedures and estimations will borrow from methods derived from process engineering [70] and managerial accounting [71–74]. Input prices (i.e., cost of each unit of resource input) will be derived from market rates when available, program budgets, or government pricing schedules (e.g., Bureau of Labor Statistics data on personnel costs for the Northeast region). The first step in the cost tracking will entail developing detailed process maps in conjunction with intervention developers and clinicians to identify all key processes [75]. The cost tracking system will track resources used to deliver the intervention as well as identify research protocol driven costs that would not be part of a real-world implementation [76]. The cost tracking system will identify intervention development costs as well as operational costs associated with running the intervention.

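### As described, the CARE effect on in-treatment progress cannot be estimated, because its only instrument, the eTPA8, is itself part of CARE

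*Protocol article*

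**What the plan says.** **The outcome.** In the Background, Hypothesis 1 names the process measures that CARE should improve: "initiation of and adherence to OUD medications, in-treatment symptom and therapeutic progress, 6-month treatment retention". Analysis and power puts the same item among the model outcomes: "treatment process quality measures (i.e., pharmacotherapy initiation and adherence, in-treatment symptom and therapeutic progress, treatment retention". The treatment effect θ is the coefficient of an indicator X, which is 0 in a clinic before CARE starts and 1 from then to the end of the study.

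**The instrument.** The Background says that the tool "monitors SUD symptoms and treatment progress indicators that are associated with clinical outcomes and relapse". Measures says: "Client-reported treatment process improvement will be computed from change scores on the eTPA8 from baseline to latest administration". No other instrument is assigned to this outcome.

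**The intervention.** The Background states: "The eTPA8 will be part of the intervention package in the current study to support QI practices". It also lists the tool as a CARE component: "4) the eTPA8 client-reported treatment progress tool to support data-driven decision making and clinic-level quality measurement". Table 1, titled "CARE intervention components during 6-month active phase", gives its execution as: "Clients complete the eTPA8 every 2 weeks; staff monitor reports for use in clinical decision making; change team uses reports for QI".

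**Timing of collection.** Data sources says that clients at the clinics taking part complete the tool every 2 weeks. It does not say whether this covers the period before a clinic starts CARE.

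**The concern.** A stepped-wedge effect is a contrast between control and intervention periods, so the outcome has to be measured in both. Here the measuring instrument arrives with the intervention. On the description given, one of the process measures in Hypothesis 1 has no comparison behind it.

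The data that would exist are change scores within CARE, from a client's first to latest completion. These mix any CARE effect with the improvement clients commonly show early in treatment, and with selection of those who stay long enough to complete the tool again. They cannot stand in for the missing contrast.

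Timing also matters. Control-phase observations cannot be recovered once a clinic has crossed over, and the Discussion plans for the first five clinics to start in December 2020 and January 2021.

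**Working it through.** The article gives no base rate, sample size or detectable difference for this outcome, so there is no figure to reproduce. The question is whether θ can be identified.

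**Step 1: the model.** From Analysis and power, with covariates Z:

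Y_ikt = μ + X_kt θ + β_t + Z_ikt + α_k + e_ikt

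**Step 2: outcome observed only under CARE.** Every observed row then has X_kt = 1, and the model reduces to

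Y_ikt = (μ + θ) + β_t + Z_ikt + α_k + e_ikt

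Only the sum μ + θ can be estimated. The column for X equals the intercept column, so θ has no estimate at all, rather than an imprecise one. Nothing in this step depends on the number of windows, sample size, intracluster correlation or significance level.

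**Step 3: numerical confirmation.** Inputs from Design and participants: 30 clinics and 6 steps of 5 clinics. Assumption: 7 windows (one all-control window plus six), because the article's text gives no number of windows and Fig. 2 is not shown. On this layout there are 30 × 7 = 210 clinic-windows, of which 5 × (6+5+4+3+2+1) = 105 have X = 1. θ is estimable only if adding X raises the rank of the fixed-effect design matrix.

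| Clinic-windows with data | Clinic effects in matrix | Rank without X | Rank with X | θ estimable |
|---|---|---|---|---|
| All 210 | no | 7 | 8 | yes |
| All 210 | yes | 36 | 37 | yes |
| 105 with X = 1 | no | 6 | 6 | no |
| 105 with X = 1 | yes | 35 | 35 | no |

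The counts depend on the 7-window assumption; the conclusion does not.

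**Step 4: full tool also run in waiting clinics.** X now varies and θ can be computed. But waiting clinics would already have the fourth CARE component, including the reports to staff, so θ would measure the rest of CARE rather than full CARE against treatment as usual.

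**Step 5: other sources.**
- The state treatment registry and Medicaid claims, as described in Data sources and Measures, do not hold the eTPA8.
- The mobile survey's listed measures do not include it. Its two cohorts are recruited when CARE starts in the clinic and 6 months later, so the 3- and 6-month follow-ups of both fall under X = 1.
- The baseline mentioned in Measures is the starting point of a client's change score, not a clinic's control phase.

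**The case against.** **Timing is not stated.** Data sources speaks of the clinics taking part, and the article elsewhere applies that term to all 30. Nothing says the tool is withheld before crossover. This stands: a reader might infer that control-phase values are certain not to exist, but the text leaves the matter open. It does not provide for them either, and Table 1 places the tool in the active phase.

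**There is a third possibility.** A reader might infer that θ fails however the tool is used before crossover. That is too strong. Table 1 defines the component as completion plus use of the reports by staff and the change team. Completion for research only, with no feedback, would withhold the active part and leave θ largely interpretable, apart from any effect of measurement itself. The article simply makes no such provision.

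**A condensed article may omit detail.** A full protocol exists and might settle the matter. But the point does not rest on an omitted detail: the article states an analysis that conflicts with its own account of the instrument.

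**The outcome is not central.** It is absent from the primary aim as worded in Analysis and power, from the overall goal given for CARE, and from the power calculations. This stands, and it limits the reach of the point.

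**Misreporting is not planned.** The article proposes no within-CARE before-after test of the eTPA8 as evidence of benefit, and Aim 2 uses its change as a predictor. Misreading is a risk to guard against, not something the plan commits to.

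**Conclusion.** The point holds for this outcome as described. If the eTPA8 is collected only under CARE, θ for in-treatment progress is not identifiable at any sample size. If the full tool with staff reports runs in waiting clinics, θ is no longer the effect of full CARE against treatment as usual.

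Two inferences carry the conclusion. The first is that in-treatment symptom and therapeutic progress means the eTPA8 change score; no sentence equates them outright, but the constructs match and no other instrument is offered. The second is that the tool is not used before CARE starts, or is used only in its full form, since the article provides for nothing else.

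A reader might infer that Aim 1 as a whole is compromised. The article does not support that. Retention, medication, overdose, hepatitis C and emergency department outcomes come from registry or claims data that exist in control periods. Aim 2 relates eTPA8 change to retention and substance use and needs no control-phase eTPA8 data.

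**What to change.** Remove in-treatment symptom and therapeutic progress from Hypothesis 1 and from the outcomes tested for a CARE effect in Analysis and power. Use the eTPA8 only for Aim 2 and for description within CARE, and state that change within CARE is not evidence of a CARE effect. This is a change of wording; its price is that one claimed process outcome becomes descriptive.

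If the sponsor wants to keep the test, the protocol must provide for TPA8 completion in control-phase clinics for research only, with no reports to staff, starting before those clinics cross over. That means extra data collection, and a possible effect of measurement itself remains.

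Substituting mobile-survey measures is not a wording change. It would mean moving the first survey cohort into the control phase, which affects recruitment of 20 clients in each of 30 clinics (20 × 30 = 600).
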